**- Sample size estimation.**

Based on previous studies of our group and previous studies for the determination of miRNAs in the presence of coronary endothelial dysfunction, we have recruited around 40-50 patients to complete the investigation (7,48–50). In our case, we will study the relationship between miRNAs and the different patterns of involvement according to the affected coronary compartment, that is, Group 1 (Macrovascular and Microvascular Angina); Group 2 (Macrovascular Angina); Group 3 (Microvascular Angina); and Group 4 (Non-coronary chest pain). Given that Group 4 corresponds to patients without coronary circulation alterations, it will be used as a control group with respect to the other groups until recruitment of 25 patients per group is completed, in a similar amount to other control groups in similar studies, totaling 100 patients. Likewise, given the possibility that some patients may present macrovascular and/or microvascular spasms that could overlap with some of the other groups, Group 5 (Macrovascular or Microvascular Spastic Angina) has been defined and will not be included for the purposes of estimating the sample size.

**- Statistical analysis.**

Continuous variables will be expressed as mean ± standard deviation (SD) or median with interquartile range (IQR), according to their distribution. As appropriate, the Mann-Whitney U test will be used to compare continuous variables, while the Chi-square test or Fisher's test will be used to compare categorical variables. If subgroup studies within each group are required (example: patients in group 1 [macrovascular angina and microvascular angina] and diabetes), the Factorial ANOVA test will be performed when equal variances are assumed or the Brown Forsythe test when unequal variances are assumed, followed by post hoc analysis with Bonferroni correction for multiple comparisons. Results will be shown as mean with a 95% confidence interval (CI). The equality of variances between groups will be calculated for each dependent variable using the Leven test, with Bonferroni correction to test for homogeneity of variance between all levels of comparison.

An alpha level of 0.05 will be used to assess statistical significance. Data will be analyzed using SPSS software or STATA.

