**HYPOTHESIS**

Different patterns of coronary artery involvement are associated with the overexpression or underexpression of specific miRNAs.

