**PRIMARY OBJECTIVE**

Characterization of miRNA expression as a function of the coronary compartment in patients with chest pain.

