**- Selection of microRNAs and other samples.**

It is essential to determine those miRNAs that have shown only over- or under-expression in previous studies of coronary atherosclerosis or stable coronary artery disease, i.e:

- Overexpression: miR-1-3p, miR-21-5p, miR-133a-3p, miR-133b-3p, miR-208a-3p,

miR-208b-3p, miR-125a-5p, miR-187-3p, miR-499a-5p, miR-502-5p.

- Under expression: miR-100-5p, miR-143-3p, miR-145-3p, miR-29b-5p.

Furthermore, since miRNA determination kits allow the analysis of multiple miRNAs in each sample, other potential candidates will be determined in agreement with the molecular biology experts. Samples corresponding to routine practice, such as blood counts, biochemistry, lipids, etc., will also be collected.

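### The primary comparison of at least 14 named miRNAs in Groups 1-3 against Group 4 is tested at a flat 0.05 with no multiplicity correction, so a false miRNA signal has roughly a 45-83% chance if nothing differs

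*Protocol*

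**What the plan says.** The primary objective reads "Characterization of miRNA expression as a function of the coronary compartment in patients with chest pain". The hypothesis is that "Different patterns of coronary artery involvement are associated with the overexpression or underexpression of specific miRNAs". Neither singles out a miRNA as primary.

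The Sample size estimation section sets four groups of 25 (100 patients) and makes Group 4 the control for Groups 1-3. Group 5, spastic angina, lies outside the sample size.

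The Selection of microRNAs section lists 10 miRNAs expected to be overexpressed and 4 expected to be underexpressed. It adds that "other potential candidates will be determined in agreement with the molecular biology experts".

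On testing, the Statistical analysis section says: "As appropriate, the Mann-Whitney U test will be used to compare continuous variables". It ends with "An alpha level of 0.05 will be used to assess statistical significance". Bonferroni is mentioned twice. The first mention depends on a condition, "If subgroup studies within each group are required", and applies to the ANOVA or Brown-Forsythe step, "followed by post hoc analysis with Bonferroni correction for multiple comparisons". The second concerns equality of variances, "using the Leven test, with Bonferroni correction to test for homogeneity of variance between all levels of comparison". No overall four-group test, testing order or false discovery rate is stated for the main comparison.

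**The concern.** The study's product will be a list of miRNAs said to be over- or underexpressed in a given coronary compartment. The hypothesis counts as supported if any miRNA reaches significance in any contrast, because no primary miRNA and no primary contrast are fixed. With each test judged separately at 0.05, the chance of at least one spurious entry grows with the number of tests.

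The section does deal with multiplicity. It places the correction on an optional subgroup step and an assumption check, and leaves the primary comparison without one.

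The Protocol itself warns that published miRNA results conflict and calls for robust methodology. A rule likely to produce a signal by chance would add to that inconsistency. It also affects what happens next: the stored samples are to be used for other biomarkers if no miRNA differences are seen, and chance findings would make that outcome less likely to be recognised.

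**Working it through.** **Inputs from the Protocol**
- Groups: 4 of 25, and 4 x 25 = 100, which agrees with the stated total. The 25 cannot be rederived, because no effect size, SD or power is given.
- Contrasts with the declared control: Groups 1, 2 and 3 each against Group 4, so 3.
- Named miRNAs: 10 + 4 = 14.
- Alpha: 0.05 per test, taken as two-sided (the Protocol does not say).

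**Number of tests and expected false positives**
- 14 x 3 = 42 tests.
- 42 x 0.05 = 2.1 expected false positives if nothing differs. This count does not depend on correlation between the tests.

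**Chance of at least one false positive**
- If all tests were independent: 1 - 0.95^42 = 0.884.
- They are not independent. The three contrasts share Group 4, and miRNAs may be correlated with one another. The Protocol gives no correlation, so it is an assumption shown over a range.
- Simulation with no true difference, 25 per group, 14 equally correlated miRNAs and 42 Mann-Whitney tests at 0.05:

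| Assumed between-miRNA correlation | Chance of at least one false positive |
| --- | --- |
| 0 | about 83% |
| 0.3 | about 77-78% |
| 0.5 | about 66-67% |
| 0.8 | about 44-45% |

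**Sensitivity to the number of miRNAs**
- The sample analysis section treats a miRNA as below the detection limit when 80% of samples are undetectable. If only 10 of the 14 survived, there would be 10 x 3 = 30 tests. The independent-test figure would be 1 - 0.95^30 = 0.785, against 0.884 for 42.
- Added candidates move the figure the other way.

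**Effect of the remedy**
- One Kruskal-Wallis test per miRNA, with Benjamini-Hochberg at 5% over the 14, brings the chance of any false positive when nothing differs to about 2-4% in simulation.

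**Cost in power, 25 v 25, two-sided t-test approximation**
- Detectable difference at 80% power: 0.81 SD at 0.05.
- At 0.05/42 = 0.00119: 1.22 SD. This is full Bonferroni, the worst case. Benjamini-Hochberg is generally less severe.

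**The case against.** **A SAP may handle this.** Multiplicity detail often sits there, and none is shown. But the Protocol is not silent. It fixes the test, the alpha and the places where Bonferroni applies, so a SAP adding control of the primary comparison would be changing a stated rule. The phrase allowing tests to be used as appropriate leaves some room, but no other test is named for this comparison.

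**The aim is descriptive.** The primary objective speaks of characterization, and treatment of epicardial lesions is decided on FFR, so no patient's care turns on a miRNA result. That limits the consequences. It does not remove them: the Protocol nowhere calls the analysis exploratory, it promises a robust assessment of expression, and it foresees less need for invasive testing.

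**The error rate is uncertain.** This stands. The list includes related pairs (133a/133b and 208a/208b), so zero correlation is the least favourable case. At 0.8 the chance falls below one half. The detection filter may also remove miRNAs.

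**Stronger readings that the documents do not support**
- A reader might infer that a two-group test is simply wrong for four groups. Group 4 is a declared control, so three two-group contrasts are a coherent design. The defect is the missing correction.
- A reader might count every pair of groups. The Protocol does not state that analysis.
- A reader might infer that a false list is certain. Even with uncorrelated miRNAs about 17% of null studies (100 - 83) would show nothing.
- A reader might extend the criticism to the Levene and Brown-Forsythe wording. Those steps belong to conditional subgroup work, the divisor for the Levene correction is not given, and the subgroup sentence is ambiguous as to layout. They do not bear on the primary comparison.

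**Conclusion.** The point holds for the primary comparison. As written, 14 named miRNAs are compared between three groups and a control at 0.05 each, with no stated correction. If nothing differs, 2.1 false positives are expected and the chance of at least one is about 45-83%, for assumed between-miRNA correlations from 0.8 down to 0.

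This rests on the 42-test count (all 14 miRNAs detectable, contrasts with Group 4 only), on two-sided testing, and on reading the two Bonferroni statements as limited to the steps they are attached to. Fewer detectable miRNAs would lower the figure and added candidates would raise it. A significant miRNA obtained under this rule could not by itself be taken as evidence for the hypothesis.

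**What to change.** In the Statistical analysis section, replace the main-comparison rule with the following, before expression is compared between groups:

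1. For each named miRNA that passes the detection filter, one Kruskal-Wallis test across Groups 1-4.
2. Benjamini-Hochberg control of the false discovery rate at 5% over those miRNAs.
3. Only for miRNAs that pass, Dunn-adjusted contrasts of Groups 1, 2 and 3 with Group 4. The 5% rate then refers to the list of miRNAs, and Dunn's adjustment covers the three contrasts within each.
4. miRNAs added to the panel, and any biomarkers measured later on the stored samples, reported as exploratory with their own correction.

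The change is to wording only and needs no new data. The price is some power: the detectable difference will lie above 0.81 SD, with 1.22 SD under full Bonferroni over 42 tests as the worst case. Because 25 per group was set by analogy with other studies and not from a target difference, the Protocol should state what difference the study can detect under the corrected rule.

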**- Selection of microRNAs and other samples.**

It is essential to determine those miRNAs that have shown only over- or under-expression in previous studies of coronary atherosclerosis or stable coronary artery disease, i.e:

- Overexpression: miR-1-3p, miR-21-5p, miR-133a-3p, miR-133b-3p, miR-208a-3p,

miR-208b-3p, miR-125a-5p, miR-187-3p, miR-499a-5p, miR-502-5p.

- Under expression: miR-100-5p, miR-143-3p, miR-145-3p, miR-29b-5p.

Furthermore, since miRNA determination kits allow the analysis of multiple miRNAs in each sample, other potential candidates will be determined in agreement with the molecular biology experts. Samples corresponding to routine practice, such as blood counts, biochemistry, lipids, etc., will also be collected.

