**- Relationship between microRNAs and cardiovascular disease: summary of the evidence.**

Currently, many miRNAs are already associated, through different pathophysiological mechanisms, with cardiovascular disease. In the following, we summarize the current evidence on the main miRNAs evaluated in clinical scenarios related to the object of our research, namely atherosclerosis and coronary artery disease.

| **miRNAs and atherosclerosis** | |
| --- | --- |
| miR-126-3p | One of the first miRNAs identified in the development of atherosclerosis.  It is highly expressed in endothelial cells and its expression is essential in vascular development.  Reduced levels favor plaque formation.  Inhibits the expression of VCAM-1, a molecule expressed by endothelial cells that allows the adhesion and migration of leukocytes to the vascular wall(28) |
| miR-21-5p | Related to the early stages of the atherosclerotic process in patients with arterial hypertension (29). |
| miR-155-5p | Expression induced by TNF-α and IFN-β. Increases the population of granulocytes and monocytes during inflammation. Also regulates the expression of the AT1R gene (angiotensin II type 1 receptor) found to be associated with the regulation of blood pressure and atherosclerosis (30). |
| miR-143-5p, miR-145-5p | They are expressed in vascular smooth muscle cells (VSMC) and inhibit migration and proliferation within the developing atherosclerotic plaque (31) |
| miR-133a-5p | Inhibits the growth and proliferation of vascular smooth muscle cells (32) |
| miR-122 -5p | It favors atherosclerosis through the regulation of cholesterol homeostasis. It also promotes inflammation and myocardial fibrosis (33) |
| miR-100-5p | It suppresses the expression of endothelial adhesion molecules attenuating the interaction between the endothelium and leukocytes and reducing inflammation of atheromatous plaques (34) |
| **miRNAs and coronary artery disease** | |
| miR-1-3p, miR-133a-3p, miR-208a-3p, miR-499a-5p | They are overexpressed in patients with acute coronary syndrome and are related to the extent of damage and the prognosis of the patient (35,36). |
| miR-126-3p, miR-17-5p, miR-92a-3p | Infra expression of these miRNAs in patients with stable coronary artery disease compared to healthy subjects (37). |
| miR-126-3p | It has shown a positive association with AMI in the general population in a 10-year follow-up (prospective study) (38) |

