**- Variability of microRNAs in published studies.**

As mentioned above, the evidence on miRNAs has increased significantly in recent years. However, it is important to note that the usefulness of miRNAs as biomarkers can vary between studies. Factors such as the clinical setting, the type of sample, as well as the time of collection and its processing, can affect the results reported in different studies (42-48). A recent meta-analysis analyzing and comparing miRNAs isolated in patients with coronary artery disease with respect to healthy subjects showed overexpression of certain miRNAs in patients with coronary artery disease, while other miRNAs showed inconsistent results with overexpression in some studies and underexpression in others (47). This study also shows interesting comparisons between miRNAs isolated in stable coronary artery disease and in acute coronary syndrome compared to healthy controls as shown in the following table.

| Coronary artery disease (any type) versus healthy controls |
| --- |
| Overexpression in coronary artery disease: miR-1-3p, miR-499a-5p, miR-133a-3p, miR-208a-3p/208b-3p, miR-21-5p, miR-142-5p, miR-145-5p |
| Over and under-expressed: miR-126-3p, miR-208b-5p, miR-92a-3p, miR-145-5p y miR-142-5p |
| Stable coronary artery disease versus healthy controls. |
| MiR overexpressed: miR-125a-5p, miR-187-3p, miR 502-5p |
| Underexpressed MiRs: miR-145-5p, miR-29b-3p, let-7 |
| Over- and under-expressed: miR-126-3p, miR-155-5p, miR-17-5p, miR-92a-3p |
| Acute coronary syndrome versus healthy controls. |
| MiR overexpressed: miR-1-3p, miR-499a-5p, miR-208a-3p/208b-3p, miR-133a-3p, miR-133b-3p, miR-27a-3p, miR-30e-5p, miR-93-5p, miR-21-5p |
| Over- and under-expressed: let-7, miR-208b-3p, miR-126-3p, miR-145-5p, miR-134, miR-223-3p, miR-142-5p |
| Acute coronary syndrome versus stable coronary artery disease. |
| Overexpressed in acute coronary syndromes: miR-21, miR-208a-3p/208b-3p, miR-133a-3p, miR-133b-3p, miR-140-5p, miR-146a-5p, miR-499a-5p, miR-27a-3p, miR-27b-3p, miR-451a, miR-29a-3p, miR-29c-3p |
| Over and under-expressed: miR-30a-5p, let-7, miR-142-5p, miR26a-5p, miR26b-5p, miR-92a-3p, miR-150-5p, miR-22-3p, miR-223-3p |

Table 8. MicroRNAs identified in patients with coronary artery disease (stable and/or acute coronary syndrome). In green microRNAs with underexpression. In red microRNAs with overexpression. In yellow microRNAs with over/under expression. (47)

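### Three of the four under-expressed candidate miRNAs carry the opposite strand from the protocol's own evidence tables, and at least two over-expressed candidates do not clearly meet the stated selection rule

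*Protocol*

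**What the plan says.** Under Selection of microRNAs and other samples, the protocol restricts the candidates to "those miRNAs that have shown only over- or under-expression in previous studies of coronary atherosclerosis or stable coronary artery disease" and then names 14. Ten are labelled over-expressed: "Overexpression: miR-1-3p, miR-21-5p, miR-133a-3p, miR-133b-3p, miR-208a-3p" and "miR-208b-3p, miR-125a-5p, miR-187-3p, miR-499a-5p, miR-502-5p". Four are labelled under-expressed: "Under expression: miR-100-5p, miR-143-3p, miR-145-3p, miR-29b-5p". The section lets further candidates be added with the molecular biology experts.

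The evidence is in two Background tables. The atherosclerosis part of Table 7 has an entry for "miR-143-5p, miR-145-5p". The row of Table 8 comparing stable coronary disease with healthy controls reads "Underexpressed MiRs: miR-145-5p, miR-29b-3p, let-7". For miR-1-3p, 133a-3p, 208a-3p and 499a-5p, Table 7 says: "They are overexpressed in patients with acute coronary syndrome and are related to the extent of damage".

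The section on collection and analysis of samples specifies RT-qPCR on custom PCR panels. The exclusion criteria rule out acute myocardial infarction with and without ST elevation.

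**The concern.** The primary objective is to characterise miRNA expression by coronary compartment, so the candidate list fixes the main measurements. On a custom panel, the name written down decides what is amplified.

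The suffix matters on the protocol's own terms. In the any-type comparison, Table 8 puts miR-208b-3p among the over-expressed and miR-208b-5p among the inconsistent. Table 7 gives miR-133a-5p and miR-133a-3p separate entries with different evidence. A change of strand is therefore a change of analyte. If the list carries the error, a null result for 145-3p or 29b-5p would not bear on the finding tabulated for 145-5p or 29b-3p.

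The second part concerns the rule. It asks for one consistent direction of expression in a stated disease setting. Some over-expressed entries draw on acute coronary syndrome, and the protocol does not say which rows of Table 8 the rule covers.

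**Working it through.** The plan states no figure to reproduce. The check matches each listed name, with its strand, against Tables 7 and 8.

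**Under-expressed candidates**

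| Listed | Listed strand in Tables 7 or 8 | Opposite strand in the tables |
| --- | --- | --- |
| 100-5p | Table 7, atherosclerosis | none |
| 143-3p | nowhere | 143-5p: Table 7, atherosclerosis |
| 145-3p | nowhere | 145-5p: Table 7; Table 8 stable row (under), any-type row (over and inconsistent), ACS row (inconsistent) |
| 29b-5p | nowhere | 29b-3p: Table 8 stable row (under) |

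Discordant strands: 3 of 4, or 3 of 10 + 4 = 14 overall.

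**Over-expressed candidates**

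- 125a-5p, 187-3p and 502-5p are in the stable row as over-expressed.
- 21-5p is in the atherosclerosis part of Table 7 without a direction. Its over-expression comes from the any-type and ACS rows.
- 1-3p, 133a-3p, 208a-3p and 499a-5p are over-expressed in the any-type row and in the ACS-versus-controls row, and are absent from the stable row.
- 208b-3p has the same over-expression listings and is also listed as over- and under-expressed in the ACS-versus-controls row.
- 133b-3p appears only in the two ACS comparisons (against controls and against stable disease).

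**Applying the rule under different readings**

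| Rows that count | Over-expressed entries failing | 145-5p | let-7 |
| --- | --- | --- | --- |
| Stable row and Table 7 atherosclerosis | 6 of 10: 1-3p, 133a-3p, 133b-3p, 208a-3p, 208b-3p, 499a-5p | meets it | meets it |
| Also the any-type row | 1 of 10: 133b-3p | fails (inconsistent) | meets it |
| Also inconsistent listings in ACS rows, counted against a candidate | 2 of 10: 133b-3p, 208b-3p | fails | fails |

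The first line accepts 21-5p on its Table 7 entry. On the stable row alone, 21-5p fails too, making 7 of 10.

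If ACS rows counted as support as well, 133b-3p would qualify, but 208b-3p would still be inconsistent. None of these readings keeps both 133b-3p and 208b-3p. The any-type row that admits 1-3p, 133a-3p, 208a-3p and 499a-5p also disqualifies 145-5p. No reading brings 143-3p, 145-3p or 29b-5p into the tables.

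**The case against.** The strongest reply is that the error may lie in the tables. The source cited for Table 7's 143/145 entry (reference 31) names both miRNAs in its title without a strand, so the suffix could have been added wrongly there. The list is also open to additions, and 11 of the 14 names have no strand conflict. All of this stands. A reader might infer that the panel measures the wrong targets, but the documents do not support that: they show a contradiction, not which side of it is wrong.

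The switch to 145-3p could also be deliberate, since Table 8 lists 145-5p as inconsistent in two rows. The protocol does not say so, and this would not explain 29b, because 29b-3p is listed only as under-expressed.

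A reader might further infer that six over-expressed candidates fail the rule. That holds only if the any-type row is not accepted as coronary atherosclerosis, a term the protocol leaves undefined. Nor does excluding infarction remove all ACS: unstable angina is not named among the exclusions.

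Two other tempting readings do not survive. A count of 5 of 14 candidates fully agreeing with the tables mixes standards, because 21-5p and 100-5p have no direction in Table 7 and no entry in the stable row. Faulting the omission of let-7 conflicts with faulting 208b-3p, since both are listed as inconsistent in the same ACS row.

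**Conclusion.** The strand contradiction is exact and needs no assumption: 3 of the 4 under-expressed candidates are listed with the strand opposite to the one in the protocol's evidence tables, and the listed strands appear in neither table.

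The selection-rule part is narrower. miR-133b-3p has ACS support only, and miR-208b-3p is inconsistent in an ACS row, so neither clearly meets the rule. For 1-3p, 133a-3p, 208a-3p and 499a-5p the answer depends on how the any-type row is classed. The number of over-expressed entries failing runs from 1 to 6 of 10 across the readings that accept 21-5p on its Table 7 entry, and reaches 7 on the stable row alone.

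Replacing the listed strands with the tabulated ones would not settle the matter. 145-5p is inconsistent in the any-type and ACS rows. For 143-5p, Table 7 describes a function in smooth muscle cells, not under-expression, and Table 8 has no entry.

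**What to change.** Before the custom panel is ordered:

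1. Check miR-143, miR-145 and miR-29b, with strand, against the sources cited for Tables 7 and 8, and correct whichever of the list or the tables is wrong. If a listed strand is intended, cite the evidence for it. If the sources do not settle it, assay both strands.
2. State whether Table 8's any-type row counts as coronary atherosclerosis, and whether listings in ACS rows count for or against a candidate.
3. Apply the rule evenly under that definition, including to 145-5p, 208b-3p, 133b-3p and let-7, and revise the list to match.

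The cost is a check of the sources and a corrected list. Because the panels are custom, a change before ordering adds no assay cost. Carrying both strands adds a few wells per sample.
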